**LIST OF ABBREVIATIONS AND RELEVANT DEFINITIONS**

| **ABR** | **General Assessment and Registration form (ABR form), the application form that is required for submission to the accredited Ethics Committee; in Dutch: Algemeen Beoordelings- en Registratieformulier (ABR-formulier)** |
| --- | --- |
| **AE** | **Adverse Event** |
| **AR** | **Adverse Reaction** |
| **CA** | **Competent Authority** |
| **CCMO** | **Central Committee on Research Involving Human Subjects; in Dutch: Centrale Commissie Mensgebonden Onderzoek** |
| **CV** | **Curriculum Vitae** |
| **DSMB** | **Data Safety Monitoring Board** |
| **GCP** | **Good Clinical Practice** |
| **GDPR** | **General Data Protection Regulation; in Dutch: Algemene Verordening Gegevensbescherming (AVG)** |
| **IB** | **Investigator’s Brochure** |
| **IC** | **Informed Consent** |
| **METC** | **Medical research ethics committee (MREC); in Dutch: medisch-ethische toetsingscommissie (METC)** |
| **(S)AE** | **(Serious) Adverse Event** |
|  |  |
| **Sponsor** | **The sponsor is the party that commissions the organisation or performance of the research, for example a pharmaceutical**  **company, academic hospital, scientific organisation or investigator. A party that provides funding for a study but does not commission it is not regarded as the sponsor, but referred to as a subsidising party.** |
| **SUSAR** | **Suspected Unexpected Serious Adverse Reaction** |
| **UAVG** | **Dutch Act on Implementation of the General Data Protection Regulation; in Dutch: Uitvoeringswet AVG** |
| **WMO** | **Medical Research Involving Human Subjects Act; in Dutch: Wet Medisch-wetenschappelijk Onderzoek met Mensen** |

**SUMMARY**

**Rationale:**

Omega-loop gastric bypass (OLGB) surgery aims to reduce weight in obese patients to a healthy BMI. Surgeons usually creat a standard length of the biliopancreatic limb (BP-limb) based on own experience. This practice leads in a substantial percentage of patients to either persisting obesity or underweight. Furthermore, a substantially percentage of patients develop disturbing diarrhea and vitamin and mineral deficiencies. The total small bowel length (TSBL) varies in subjects between less than 5 to more than 10 meters. This variance could have consequences both for weight loss and deficiencies after OLGB. The aim of the study is to investigate whether adjusting the length of the BP-limb tot the TSBL leads to more weight loss with smaller variance and to less bowel movements and less deficiencies of vitamins and minerals using an optimal multivitamin Fitforme WSL primo.

**Objective**:

Primary :

To compare the percent total weight loss (%TWL) at 5 years between the group with the standard BP-length and the group with an adjusted BP-length.

Secondary :

To compare the proportion of patients with a BMI between 22 and 30 Kg/m^2^,the mean number of daily bowel movements and number of days with daily bowel movements > 3 over in the last two weeks before a visit, Quality of life measured by the RAND-36 questionnaire between the groups and the percentage of patients experiencing moderate to severe dumping symptoms defined by the Dumping Severity Score (DSS) between the groups.

To compare the proportion of patients in the two groups who have neither deficiencies of iron, nor vit. D, nor vit B12 without extra suppletion, during the study

**Study design:** double blind intervention study

**Study population:**

Patients between 18 and 65 years with obesity class III or II with comorbidity (based on the IFSO criteria and Dutch guideline on obesity), scheduled for OLGB surgery and willing to participate.

**Intervention** :

OLGB : patients will be randomly allocated to either a standard BP-limb of 150 cm or to a BP-limb length based on their TSBL : TSBL < 500 cm : BP-limb : 150 cm ; TSBL 500-700 cm : BP-limb 180 cm ; TSBL > 700 cm : BP-limb : 210 cm.

**Main study parameters/endpoints:**

Percent total weight loss (%TWL) at 5 years.

Proportion of patients with 22 ≤ BMI ≤ 30 Kg/m^2^

Mean number of daily bowel movements in the last two weeks

Mean number of days with daily bowel movements > 3 in the last two weeks

Quality of life measured by the RAND-36 questionnaire

Percentage of patients experiencing moderate to severe dumping symptoms defined by the Dumping Severity Score (DSS)

Percentage of patients who have neither deficiencies of iron, nor vit. D, nor vit B12 without extra suppletion

**Nature and extent of the burden and risks associated with participation, benefit and group relatedness:**

Measuring TSBL will take 10 minutes of extra time during the surgery and increases slightly the risk of damaging the intestine. Bariatric surgeons are experienced in measuring small bowel. Patients have 4 extra visits in 5 years and during routine blood testing an extra bloodsample of 20 ml will be drawn for research purposes. They have to fill in 2 questionnaires at their visits. Benefit is a free providing of a daily multivitamin capsule during the study and possibly a better outcome after surgery in terms of weight loss and side effects.

# INTRODUCTION AND RATIONALE

Omega-loop gastric bypass, also known as mini-gastric bypass (OLGB/MGB) is currently one of the most effective treatment options for morbid obesity. It is technically a more simple procedure compared to the RYGB and has proven in some studies to have a better outcome in terms of weight loss and reduction of co-morbidities.

The aim of the weight loss surgery is to achieve an optimum weight loss aiming at a BMI of 25 kg/m^2^ in combination with a minimum of side effects, like vitamin, macronutrient, mineral deficiencies and diarrhea.

There is substantial variation in the determination of the biliopancreatic (BP) limb length with some surgeons using a fixed length and some a length based on the initial BMI. The length varies between less than 150 cm to more than 250 cm. A recent retrospective study by Charalampos et.al. adjusting limb length from 200 to 300 cm depending on BMI resulted in on average comparable EWL when corrected for initial BMI. The average BMI after 36 months was 27.5 Kg/m2 (± 5.3). This strategy of BP based on initial BMI results in 16% of patients with a final BMI > 33 and 16% with less than 22.

Furthermore despite the advice to take life-long (over-the-counter) multivitamin suppletion 20% or more patients developed de novo deficiencies of iron, vit B12, vit D, and/or minerals in the first postoperative year (1).

Ahuja et.al. adjusted the limb length from 150 to 250 cm depending on BMI and also found increasing number of deficiencies of micro-nutrients with increasing BP length (2). In this study patients were advised to use a multivitamin supplement, however no specific brand was used.

Some evidence exists in RYGB surgery that the length of the BP-limb influences weight loss. Nergaard et al. performed a RCT comparing a RYGB with a BP-limb of 200 to 60 cm with a RYGB with an alimentary limb of 60 and 150 cm respectively. The longer BP-limb length led to more weight loss but also to more bowel movements and micronutrient deficiencies (3). Total small bowel length was measured in their whole patient population and varied between 480 and 870 cm but was not taken in to account in terms of stratification.

Zorilla et.al performed a systematic review on limb length in RYGB and found 13 studies meeting adequate quality (4). Weight loss on the whole was better in patients with longer BP limbs.

Earlier studies showed that the length of the common channel plays a role in the outcome of surgery both in weight loss and in micronutrient deficiencies. The length of the total small bowel can vary considerably with measured values between 350 to more than 1000 cm (5).

In this study of Tacchino in 443 patients TSB median length was 690 cm (women 678±92, men 728±85 cm) with a SD of 94 cm. In males 3% had a bowel length < 400 cm and 15% > 800, in females 2% had a length of < 400 cm and 5% > 800 cm.

In current practice in OLGB surgery surgeons use a fixed BP-limb length or adjust the length to the initial BMI. Total weight loss varies in literature between 30-35 % with SD up to 8.5%, aiming at a BMI result between 23 and 30 Kg/m^2^

The contribution of the length of the residual small bowel, total minus the BP-limb, on weight loss and deficiencies has up till now not been studied in OLGB surgery.

# OBJECTIVES

To investigate whether adjusting the length of the BP-limb of the OLGB based on measured total small bowel length leads to more weight loss, resolution of co-morbidities with less development of micronutrient deficiencies and bowel movements compared a to a standard limb length in OLGB in patients using a standardized multivitamin supplement (FitForMe Primo).

**Primary Objective**:

To compare the percent total weight loss (%TWL) at 5 years between the group with the standard BP-length and the group with a adjusted BP-length .

**Secondary Objective(s):**

1) To compare the percent of total weight loss (%TWL) between the groups at 1,2,3 and 4 years.

2) To compare the percent excess weight loss (%EWL) between the groups at 1,2,3, 4 and 5 years.

Definition: %EWL (Initial Weight – Postop Weight) / (Initial Weight – Ideal Weight)

(ideal weight is defined by the weight corresponding to a BMI of 25 kg/m2 )

3) To compare the percent excess BMI loss (%EBMIL) between the groups at 1,2, 3, 4 and 5 years.

Definition: %EBMIL (ΔBMI / (Initial BMI – 25)) * 100)

4) To compare the proportion of patients with 22 ≤ BMI ≤ 30 between the groups at 1,2 3, 4 and 5 years.

5) To compare the mean number of daily bowel movements and number of days with daily bowel movements > 3 in the last two weeks, between the groups at 6 months, 1,2, 3, 4, and 5 years.

6) To compare the Quality of life measured by the RAND-36 questionnaire between the groups at 6 months, 1,2, 3, 4 and 5 years, absolute and compared to before surgery

7) To compare the percentage of patients experiencing moderate to severe dumping symptoms defined by the Dumping Severity Score (DSS) (see Emous et al.) at 6 months, year 1, 2, 3, 4 and 5 between the groups, absolute and compared to before surgery.

8) To compare the proportion of patients in the two groups who have neither deficiencies of iron, nor vit. D, nor vit B12 without extra suppletion, at 6 months, 1, 2, 3, 4 and 5 years. Deficiencies are defined by the lower border of the local normal laboratory values.

9) To compare the proportion of patients in the two groups who have a deficiency at 6 months, 1, 2, 3, 4 and 5 years, or received extra suppletion for :

- Vitamin B1

- Vitamin B6

- Folic acid

- Vitamin A

- Vitamin D

- Calcium

- Phosphate

- Albumin

- Zinc

- Copper (visit 1,3,5 years)

- Selenium (visit 1,3,5 years)

Deficiencies are defined by the lower border of the local normal laboratory values.

10)To compare the proportion of patients between the groups at 1, 2, 3, 4 and 5 years without diabetes, both those with remission of diabetes and those without de novo diabetes, defined as an HbA1c less than 48 mmol/mol without diabetes medication in the last 6 months. ^#^

11) To compare the proportion of patients between the groups at 1, 2, 3,4 and 5 years with improvement of diabetes, defined as a reduction of HbA1c with at least 10 mmol/mol, but not reaching remission criteria and/or less anti-diabetic medication ^#^.

12) To compare the proportion of patients between the groups at 1, 2, 3, 4 and 5 years with remission of hypertension, defined as a blood pressure of 140/90 mmHg or less without antihypertensive medication ^#^.

13) To compare the proportion of patients between the groups at 1, 2, 3, 4 and 5 years with improvement of hypertension, defined as a lower blood pressure of at least 10 mm Hg systolic and/or 5 mmHg diastolic, and/or less antihypertensive medication (not reaching the criterion of remission) ^#^.

14) To compare the proportion of patients between the groups at 1, 2, 3, 4 and 5 years with resolution of sleep apnea, defined by cessation of CPAP or other devices use, documented by their own pulmonologist

15) To perform analysis of the above parameters in the subgroups with TSBL 500-700 and >700.

16) To compare within the standard group of patients with an allocated BP-limb length of 150 cm those with a TSBL < 500 to those with a TSBL 500-700 and to those with TSBL >700 cm on the above mentioned parameters.

^#^ : patients are asked to bring along with their visit an overview of current medication from their local pharmacist and actual use will be checked with the patient. In case of absence of the overview, after informed consent is given, the local pharmacist will be asked to provide the investigator with an overview of the medication

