### Secondary study parameters/endpoints

1) Percent of total weight loss (%TWL) at 1,2,3,and 4 years.

2) Percent excess weight loss (%EWL) at 1,2,3, 4 and 5 years.

Definition: %EWL (Initial Weight – Postop Weight) / (Initial Weight – Ideal Weight)

(ideal weight is defined by the weight corresponding to a BMI of 25 kg/m2 )

3) Percent excess BMI loss (%EBMIL) at 1,2,3, 4 and 5 years.

Definition: %EBMIL (ΔBMI / (Initial BMI – 25)) * 100]

4) Proportion of patients with 22 ≤ BMI ≤ 30 Kg/m^2^ at 1,2,3, 4 and 5 years

5) Mean number of daily bowel movements in the last two weeks at 6 months, 1,2,3, 4 and 5 years.

6) Mean number of days with daily bowel movements > 3 in the last two weeks at 6 months, 1,2,3, 4 and 5 years.

6) Quality of life measured by the RAND-36 questionnaire at 6 months, 1,2,3, 4 and 5 years, absolute and compared to before surgery.

7) percentage of patients experiencing moderate to severe dumping symptoms defined by the Dumping Severity Score (DSS) at 6 months, 1,2,3, 4 and 5 years, absolute and compared to before surgery.

Moderate to severe is defined as 3 or more dumping symptoms with a severity score of 2 or 3 on a 4-point Likert scale. Symptoms are divided in two categories, e.g. early and late,

as described by Emous et.al. (7)

8) percentage of patients who have neither deficiencies of iron, nor vit. D, nor vit B12 without extra suppletion, at 6 months, 1,2,3, 4 and 5 years . Deficiencies are based on the local normal laboratory values.

9) Proportion of patients who have a deficiency at 6 months, 1,2,3, 4 and 5 years, or received extra suppletion for:

- iron (ferritin)

- vitamin B_12_

- vitamin D_3_

- Vitamin B_1_

- Vitamin B_6_

- Folic acid

- Vitamin A

- Vitamin D

- Calcium

- Phosphate

- Albumin

- Zinc

- Copper at 1,3 or 5 years

- Selenium at 1,3 or 5 years

10)Proportion of patients at 1,2,3, 4 and 5 years without diabetes, both with remission and without de novo, defined as an HbA1c less than 48 mmol/mol without diabetes medication in the last 6 months.

11)Proportion of patients at one year and two years with improvement of diabetes, defined as a reduction of HbA1c of 10mmol/mol or more but not reaching remission criteria and/or less anti-diabetic medication.

12)Proportion of patients at 1,2,3, 4 and 5 years with remission of hypertension, defined as a blood pressure of 140/90 mmHg or less without antihypertensive medication.

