13)Proportion of patients at 1,2,3, 4 and 5 years with improvement of hypertension, defined as a lower blood pressure and/or less antihypertensive medication (not reaching the criterion of remission).

14)Proportion of patients at 1,2,3, 4 and 5 years with resolution of sleep apnea, defined by cessation of CPAP or other devices use, documented by their own pulmonologist

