## Study procedures

A standard operation protocol for OLGB will be used in all patients. The pouch will be made with the help of a linear stapler. At first, the stomach will be transected horizontally at the junction of the corpus and antrum at the level of crow’s foot. A small pouch is made with help of a calibration sonde of 34 French, the pouch is finished near the angle of His. Then the total limb length is measured. With a succesfull TSBL measurement the OR nurse will open the envelop and the allocated procedure will be communicated to the surgeon. Based on the randomization outcome biliopancreatic limb length is measured. In case the measurement of the total limb length does not succeed, standard limb length of 150 cm is performed. An antecolic, retrogastric anastomosis is performed by liniar stapling and the remaining defect is closed by V-loc. An anti-reflux stitch is performed. Integrity of the anastomoses is checked by methylene-blue-test and in case of leakage, extra sutures will be applied. The mesenterial defect of Peterson will be closed as far as possible by endo hernia stapling or unresolvable V-loc.

The extra measurements of limb length will take less than ten minutes of time. In patients allocated to standard treatment the surgeon will construct a BP-limb of 150 cm. In patients allocated to the adjustment length, the length of the BP-limb will depend on the total small bowel length : < 500 cm : 150 BP; 500-700 cm : 180 BP and > 700 cm : 210 BP.

On leave of the hospital the patients will be provided with Fitforme WSL Primo multivitamin capsules for the following period and will be instructed to use one capsule once daily.

Follow-up will take place in accordance with usual care, i.e. after 1,6,12 and 24 months and yearly up till 5 years. Extra visits will be at 18,30,42 and 54 months for compliance check and distribution of FFM multivitamins.

Weight measurements and blood samples will be taken in accordance with the standard protocol of follow-up after bariatric surgery in our institute added with 20 ml for selenium and copper measurements and future lab tests at 1,3 and 5 years.

Data from 6,12 and 24 months and every year thereafter up to five years after surgery will be anonymously collected in a database.

At each visit standard care includes :

- inquiry after well being and complaints, side effects, adverse events
- documenting current medication use, both regular and over-the-counter, and when applicable CPAP use

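### The improvement rules for hypertension and diabetes count falls achieved on added drugs, and drug reductions with worse control, as improvement

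*Protocol*

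**What the plan says.** Protocol section 2, objective 13: improvement of hypertension is "defined as a lower blood pressure of at least 10 mm Hg systolic and/or 5 mmHg diastolic, and/or less antihypertensive medication", with the restriction "not reaching the criterion of remission". Section 7.1.2, item 13, gives the matching endpoint as "defined as a lower blood pressure and/or less antihypertensive medication (not reaching the criterion of remission", with no mmHg threshold.

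Objective 11: improvement of diabetes is "defined as a reduction of HbA1c with at least 10 mmol/mol, but not reaching remission criteria and/or less anti-diabetic medication". Section 7.1.2, item 11, reads "defined as a reduction of HbA1c of 10mmol/mol or more but not reaching remission criteria and/or less anti-diabetic medication".

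The remission rules are built differently. Objective 12 requires control and absence of drugs together: "defined as a blood pressure of 140/90 mmHg or less without antihypertensive medication". Objective 10 does the same with HbA1c.

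Medication is known at each visit: standard care includes "documenting current medication use, both regular and over-the-counter, and when applicable CPAP use" (Study procedures), supported by a pharmacy overview. Section 9 compares qualitative secondary endpoints by Fisher's exact or chi-square test.

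**The concern.** The limbs are alternatives, and none is conditional on the others. Nothing requires medication to be stable when the measurement falls, or the measurement to hold when medication is cut. Nor does anything stop one blood pressure component from rising while the other falls. The stated aim in section 2 is resolution of co-morbidities after surgery, and the remission rules show that the authors know control and medication must be read together.

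The stake is the between-arm comparison. Drugs are added because control is poor and withdrawn because it is good. If surgery affects control differently in the two arms, the discordant patients will not be spread evenly. Blinding does not prevent this, because the prescriber reacts to the reading and not to the allocation. A simple comparison of proportions cannot correct it.

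**Working it through.** **Step 1. Apply the rule as written.** The documents attach no figure to these endpoints, so there is none to reproduce. For objective 13: improved = not in remission AND (systolic change ≤ −10 OR diastolic change ≤ −5 OR fewer drugs).

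| Before → after | Drugs | Objective 13 |
|---|---|---|
| 160/95 → 145/87 (−15/−8) | 1 → 3 | improved |
| 145/88 → 165/98 (+20/+10) | 2 → 1 | improved |
| 145/88 → 165/98 (+20/+10) | 1 → 0 | improved |
| 150/92 → 165/87 (+15/−5) | 1 → 1 | improved |
| 150/92 → 150/92 | 1 → 2 | not improved |
| 150/92 → 155/95 (+5/+3) | 1 → 2 | not improved |
| 150/92 → 147/90 (−3/−2) | 1 → 1 | not improved (improved under item 13) |

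Under objective 11, HbA1c 70 → 58 mmol/mol after a second drug is added is a fall of 12 without remission, hence improved. This step needs no assumption.

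**Step 2. Illustrate the effect on a comparison.** All inputs are assumptions, since the documents give no blood pressure spread and no drug-change rates: SD 9/6 mmHg at each visit; systolic–diastolic correlation 0.6; an added drug lowers pressure by 10/5; a reduction leaves mean pressure unchanged; no direct surgical effect; remission ignored. The SDs of change are 9√2 = 12.7 and 6√2 = 8.5.

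Probability of being scored improved, written rule:
- unchanged drugs: P(systolic ≤ −10 or diastolic ≤ −5) = 0.363 (0.30 at SD 7/5, 0.43 at SD 12/8);
- drugs added: 1 − [1/4 + arcsin(0.6)/2π] = 1 − 0.352 = 0.648;
- drugs reduced: 1.

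With no-worsening conditions (as under the fix):
- unchanged drugs: 0.363 less the 0.020 in whom the other component rose by its threshold = 0.343;
- drugs added: 0;
- drugs reduced: P(systolic rise < 10 and diastolic rise < 5) = 1 − 0.363 = 0.637, by symmetry.

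With a share *i* intensified and *r* reduced:
- written rule: 0.648*i* + *r* + 0.363(1 − *i* − *r*);
- conditional rule: 0.637*r* + 0.343(1 − *i* − *r*).

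First row, experimental arm, written rule: 0.648×0.05 + 0.20 + 0.363×0.75 = 0.505.

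| Experimental *i*/*r* | Control *i*/*r* | Written rule | Difference | Conditional rule | Difference |
|---|---|---|---|---|---|
| 5%/20% | 20%/10% | 50.5% v 48.4% | +2.1 | 38.5% v 30.4% | +8.1 |
| 5%/15% | 20%/15% | 47.3% v 51.6% | −4.3 | 37.0% v 31.9% | +5.1 |
| 5%/40% | 10%/10% | 63.2% v 45.5% | +17.7 | 44.3% v 33.8% | +10.5 |

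If a reduction instead raises mean pressure by 10/5, 0.637 becomes 0.352 and the conditional differences become +5.2, +5.1 and +2.0. The written-rule differences do not change.

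**Step 3. A second model, with a direct effect.** Assumptions: systolic pressure only, baseline mean 148 (SD 14), surgical fall 15 v 8 mmHg, 9 mmHg per added drug, drugs added with probability 0 to 0.9 above 140 mmHg, and drugs cut with probability 0.2 or 0.6 at low pressures. The comparison rule allowed no added drugs on the pressure limb and no rise on the medication limb. The written rule narrowed the gap by 0.2 points (23.0 v 23.2; no additions, cut 0.2) to 2.9 points (10.0 v 12.9; addition 0.9, cut 0.6). None of the eight combinations reversed it.

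**The case against.** A reader might infer that the rule systematically rewards the arm needing more medication and so pulls the comparison towards no difference. The documents do not support that. An added drug scores only when the measurement also reaches its threshold. The less-medication limb works the other way: it credits every reduction, and reductions are likelier in the arm with better control. In the third row of the table intensification is commoner in the control arm, yet the written rule inflates the experimental advantage. The reversal in the second row arises in a model with no direct surgical effect; the model that has one showed only modest narrowing. This part of the objection stands, and no direction of bias is claimed.

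It is also fair that these are two among many secondary endpoints, that remission is analysed separately under a sound rule, and that derivation detail often sits in an analysis plan, which is not shown here. The first two limit the importance. The third does not remove the point: the protocol does not leave the classification open. It writes out a rule that gives the results in step 1.

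Finally, the protocol does not say that drug dose is recorded, so a fix must not depend on it. That stands too.

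**Conclusion.** The point holds as a misclassification built into four written definitions. That part rests on the text alone. Its effect on the between-arm difference can be dilution, reversal or inflation. The size and sign depend on how often drugs are added or reduced in each arm and on how far pressure or HbA1c moves when they are, none of which the documents give. The percentages above are illustrations, not forecasts, and the conditional rule is a comparator rather than the truth: it leaves most of the measurement noise in place (0.343 v 0.363 among patients with no change at all).

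The damage is confined to the improvement endpoints for hypertension and diabetes. The remission endpoints, the primary %TWL analysis and the sample size are untouched. The definitions should be corrected, but this does not threaten the trial's main conclusion.

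**What to change.** In objectives 11 and 13 and in section 7.1.2 items 11 and 13, add a no-worsening condition to each limb. This concerns outcome classification only, not patient care.

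- Measurement limb: count the fall only if the relevant medication has not increased compared with before surgery. For hypertension, also require that the other blood pressure component has not risen by its own threshold (10 mmHg systolic, 5 mmHg diastolic).
- Less-medication limb: count the reduction only if blood pressure has not risen by 10 mmHg systolic or 5 mmHg diastolic, or HbA1c by 10 mmol/mol.
- State what counts as more or less medication in terms that the medication overview can support, and make clear that the remission exclusion applies to both limbs of the diabetes rule.

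Two separate contradictions must be reconciled in the same edit. Item 13 lacks the thresholds of objective 13. Item 11 is limited to two visits ("Proportion of patients at one year and two years with improvement of diabetes"), whereas objective 11 covers 1 to 5 years. Resolving these alone would not cure the present problem.

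Fix the wording before the first unblinded yearly interim comparison under section 9.4. The cost is an amendment to two definitions, each in two places, and somewhat longer derivation code. Blood pressure, HbA1c and medication use are already collected. The downside is fewer patients counted as improved in both arms: in the first illustrative row, 38.5% instead of 50.5% and 30.4% instead of 48.4%.

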## For qualitative parameters (categorical or ordered), frequency counts and percentages of each category will be calculated by treatment group. Percentages will be reported up to 1 decimal place.

## Primary study parameter(s)

The primary null hypothesis for this study is that there is no significant difference in the mean change in the percent of total weight loss (%TWL) at five years, between patients treated with a TSBL adjusted BP limb length (active group) versus patients treated with a standard BP limb length of 150 cm (control group).

In addition to the descriptive statistics (see the above section : Patient demographics other baseline characteristics), the two treatment strategy groups will be compared using two-sample T-test if parameter is normally distributed. Visual inspection of the distribution, as well as the Shapiro-Wilk test for normality, will used to assess normality. Unless equality of variance between groups is established, the Satterthwaite method for t-statistics and 95% confidence intervals will be used. If data is skewedly distributed, a Mann-Whitney U-test (Wilcoxon two-sample test) will be applied. For the difference in medians, the Hodges-Lehmann estimate will be used with distribution-free 95% confidence intervals.

In addition to the above mentioned analyses, the homogeneity of treatment effect over different strata of patients will be evaluated. In this, differences in treatment effect over separate strata of potentially relevant factors (e.g. gender, baseline BMI, co-morbidities, compliance, etc) will be evaluated. A multivariable model will be used to formally establish homogeneity, i.e. the absence of effect modification for the potentially relevant factors, separately.

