## Secondary study parameter(s)

All secondary endpoint parameters (quantitative and qualitative) will be presented as described in section : Patient demographics other baseline characteristics.

For the evaluation of differences between groups, the primary analysis approach will be applied for the quantitative secondairy endpoint parameters..

For the qualitative parameters a Fisher exact test or a Chi-square test will be used.

For the parameters related to the occurrence of side effects, the evaluation focusses on the “absence” of differences. For these analysis estimates of risk differences with 90% confidence intervals, based on the Farrington-Manning Method will be used (non-inferiority setting, one sided approach). Due to sample size constraints, formal hypothesis tests on non-inferiority will not be performed. Multivariable logistic (or log-binomial) regression modelling is not foreseen.

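### Objective 16 is an observational comparison of bowel-length classes, but the only tests stated for secondary parameters are unadjusted, so a sex difference in outcome could be read as a bowel-length effect

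*Protocol*

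**What the plan says.** Section 2, Secondary Objective(s), item 16 sets out "To compare within the standard group of patients with an allocated BP-limb length of 150 cm". It then defines three classes by bowel length and covers all the outcomes listed before it. Everyone in this comparison has the same limb length, and class membership is decided by anatomy.

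Section 9 names no test for this objective. Its general rules are:
- Quantitative secondary parameters: "the primary analysis approach will be applied for the quantitative secondairy endpoint parameters". Under Primary study parameter(s) that approach reads "the two treatment strategy groups will be compared using two-sample T-test if parameter is normally distributed", with a Mann-Whitney test for skewed data. No covariate is named.
- Proportions: "For the qualitative parameters a Fisher exact test or a Chi-square test will be used".
- At the end of the paragraph on side effects: "Multivariable logistic (or log-binomial) regression modelling is not foreseen".

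Sex appears in Section 9 in two roles. It is a baseline characteristic tabulated by treatment strategy group, and it is a possible modifier of the randomised treatment effect. A further clause lets the methods be modified for relevant baseline differences, but it concerns the randomised groups.

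The Introduction, citing a series of 443 patients, reports "TSB median length was 690 cm (women 678±92, men 728±85 cm) with a SD of 94 cm".

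**The concern.** A t-test or chi-square test between randomised arms needs no adjustment to be free of systematic confounding. The same test between anatomical classes has no such protection. The Introduction puts the male mean 50 cm above the female mean, and the 700 cm cut lies between the two (678 and 728 cm). The two larger classes should therefore differ in their proportion of men. If men and women also differ in weight loss or in deficiency rates, an unadjusted class difference mixes that with any effect of bowel length.

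This matters because the Introduction describes the role of residual bowel length in this operation as unstudied, and objective 16 looks at it with limb length held fixed. Baseline tables by treatment group would not show a sex imbalance between TSBL classes.

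**Working it through.** **Reproducing the plan's own figure.** The Protocol gives no figure for objective 16. Its sample size supplies the SD and the number used below. For 5 points, SD 12, two-sided alpha 0.05 and 80% power, the normal formula gives n = 2 × (1.960 + 0.842)² × 12² / 5² = 90.4, so 91 per arm. With the noncentral t, 92 per arm gives 80.3% power, and SDs of 12 and 9 give 88.9% (stated: 88.8%). These figures reproduce.

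**Inputs.** From the Introduction: women 678 (SD 92) cm, men 728 (SD 85) cm. From Section 4.4: SD of %TWL 12, and 92 evaluable patients in the standard arm. Assumptions: TSBL is normal within each sex, and the male share is 24%. That share comes from treating 690 cm as the overall mean: (690 − 678)/(728 − 678) = 0.24. I also tried 10% to 50%.

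**Step 1. Class probabilities by sex.**
- Above 700 cm: men 1 − Φ((700 − 728)/85) = 0.629; women 1 − Φ((700 − 678)/92) = 0.406.
- 500-700 cm: men 0.367; women 0.568.
- Below 500 cm: men 0.004; women 0.027.

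**Step 2. Male share per class at 24% men.**
- >700 cm: 0.24 × 0.629 / (0.24 × 0.629 + 0.76 × 0.406) = 0.151/0.459 = 33%.
- 500-700 cm: 0.24 × 0.367 / (0.24 × 0.367 + 0.76 × 0.568) = 0.088/0.520 = 17%.
- Difference: 16 points (8 to 22 points for 10% to 50% men).

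**Step 3. Class sizes among 92 patients.** >700 cm: 92 × 0.459 = 42. 500-700 cm: 92 × 0.520 = 48. <500 cm: 92 × 0.021 = about 2.

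**Step 4. Bias in %TWL, >700 versus 500-700 cm.** Bias = 0.159 × sex difference. The standard error is 12 × √(1/47.8 + 1/42.2) = 2.5 points.

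| Assumed sex difference (points) | Bias (points) | False-positive rate of a 5% test |
|---|---|---|
| 2 | 0.3 | 5.2% |
| 5 | 0.8 | 6.1% |
| 8 | 1.3 | 7.9% |

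Over 10% to 50% men and 2 to 8 points, the bias runs from 0.2 to 1.7 points.

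**Step 5. Bias in iron-deficiency risk.** Assumed sex risk differences of 10, 20 or 30 points give 0.159 × these = 1.6, 3.2 or 4.8 points. With an assumed risk of 20%, the standard error is √(0.2 × 0.8 × (1/47.8 + 1/42.2)) = about 8 points.

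**Step 6. Does the normal model hold?** Not in the tails. The Protocol reports "In males 3% had a bowel length < 400 cm and 15% > 800, in females 2% had a length of < 400 cm". Its figure for women above 800 cm is 5%. The model gives 0.006% of men and 0.1% of women below 400 cm, and 20% of men and 9% of women above 800 cm. The direction at the long end does not depend on the model (15% against 5% above 800 cm). At the short end the reported figures show no shortage of men (3% against 2% below 400 cm), so the sex gradient is supported for >700 versus 500-700 cm only. The count below 500 cm is rough.

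**The case against.** The strongest reply is that the Protocol never chose unadjusted tests for objective 16. The objective is missing from the numbered endpoints in Section 7.1.2, it has three classes rather than two groups, and covariates for a late secondary objective are often left to the SAP. This stands in part: the unadjusted tests reach objective 16 only through the general rule in Section 9. But that rule is the only one stated, and it does not suit a non-randomised contrast.

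Four stronger readings are tempting and are not supported:
- A reader might infer that known sex differences in weight loss and iron status will be mistaken for bowel-length effects. The Protocol states no sex difference in any outcome. Deficiency is also judged against local laboratory limits, and if these are sex-specific, which is not stated, the iron component could be smaller.
- A reader might take "Multivariable logistic (or log-binomial) regression modelling is not foreseen" as a bar on regression here. The sentence belongs to the side-effects paragraph. Linear models are not excluded, and a multivariable model is planned for the primary endpoint.
- A reader might think objective 16 is the only analysis that bears on residual bowel length. The randomised comparison and objective 15 also vary it, through limb length.
- A reader might conclude that the classes should give way to continuous TSBL. The classes match the allocation rule, so a class contrast validly describes how each class fares with 150 cm. A linear term would impose linearity, and logistic models with several covariates could be unstable with sparse events.

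It is also fair to say that the bias is small against sampling error.

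**Conclusion.** The point holds in a limited form. Objective 16 is an observational contrast, the stated methods are unadjusted, and the Protocol's own bowel-length figures imply more men in the >700 cm class than in the 500-700 cm class. Confounding by sex is therefore possible but not shown, because its second link, a sex effect on outcome, is an assumption throughout. At 24% men and an assumed 2 to 8 points, the bias in %TWL is at most about half a standard error (1.3/2.5). The expected handful of patients below 500 cm limits objective 16 more than the confounding does. The randomised primary analysis is not touched. This is a low-priority improvement.

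**What to change.** Add a short paragraph to Section 9 for objective 16:
- Keep the three TSBL classes.
- Compare quantitative outcomes between 500-700 and >700 cm by linear regression adjusted for sex and baseline BMI, both of which Section 9 already lists as potentially relevant.
- Compare proportions by sex-stratified risk differences, for example Mantel-Haenszel.
- Present the <500 cm class descriptively.
- Label all results as an exploratory observational association.
- Optionally, add regression on continuous TSBL as a supplement.

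No new data are needed: weight, height and gender are already recorded. The loss of precision from adjusting for sex is slight. The correlation between class and sex is 0.159 × √(0.469 × 0.531 / (0.244 × 0.756)) = 0.185, where 0.469 is the >700 cm share and 0.244 the male share of these two classes. The standard error therefore grows by a factor 1/√(1 − 0.185²) = 1.018, from 2.5 to about 2.6 before any gain from baseline BMI. The real cost is a little more analysis and some instability for rare outcomes, since the male stratum would hold only about 8 (92 × 0.088) and 14 (92 × 0.151) patients in the two classes.
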